**Fig. 2 Fig2:**
[figure not shown]
IDEA Study SMART Design

## Methods: participants, interventions, and outcomes

### Study setting {9}

The study will take place at Sinai Chicago in Chicago, Illinois, USA. Sinai Chicago is the largest private safety-net health system in Illinois and includes three hospitals: Mount Sinai Hospital (MSH), Holy Cross Hospital (HCH), and Schwab Rehabilitation Hospital. More than 100,000 people with diabetes live in Sinai Chicago’s primary service area, and approximately 70% of all Sinai Chicago patients live with diabetes or prediabetes. Communities in Sinai Chicago’s primary service area have some of the most severe disparities related to diabetes incidence, control, and complications. In Mount Sinai Hospital’s 2022 Community Health Needs Assessment, diabetes was the fifth most important community health need according to more than 560 surveyed individuals in the service area [19]. Specifically, the study will take place at two Center sites, one at MSH and one at HCH. The Center was launched in September 2020 to treat patients with pre-diabetes, diabetes, and other endocrine disorders. The Center is a robust, patient-centered Diabetes Center of Excellence with coordinated care amongst several clinicians.

### Eligibility criteria {10}

Eligibility criteria for each study component (SMART, participant focus group discussions, and staff interviews) are described in Table 1.

**Table 1 Tab1:** IDEA study eligibility criteria

Study component	Inclusion criteria	Exclusion criteria
SMART	• Diagnosed with type 1 or type 2 diabetes • 18 years of age or older • Able to provide informed consent • African American/Black or Latine • HbA1c level ≥ 7% measured within 365 days prior to study enrollment • Have a smartphone compatible with the Glooko RGM application [20] • Completed at least one appointment at the Center since the Center opened in 2020 • Fluent in English or Spanish	• Have an activated Power of Attorney • Diagnosed with Stage V renal disease or undergoing dialysis • Diagnosed with a severe form of cardiovascular disease • Diagnosed with gestational diabetes only (without type 1 or type 2) • Diagnosed with any severe form of mental disorder including schizophrenia, bipolar disorder, or severe depression • Pregnant • Diagnosed with Alzheimer’s disease or dementia • Already an active user of RGM • Actively working with a CHW for their diabetes • Planning to travel outside of the Chicagoland area for more than three months in the year following study enrollment • Use a continuous glucose monitor that is incompatible with the Glooko RGM application
Participant Focus Group Discussions	• Meet all eligibility for SMART component of study • Completed at least 3 months of their assigned SMART study condition	None
Center Staff Interviews	• Employed by the Center during the study period • 18 years of age or older • Able to provide informed consent • Fluent in English or Spanish	None

### Who will take informed consent? {26a}

Participants who are deemed eligible based on the above eligibility criteria, and agree to be randomized, will provide written informed consent before participating in the study. During the informed consent process, a member of the research team will explain the study in detail, including its objectives, the funding source, who is being invited to participate, what will take place in each study arm, the duration of the study, and how many people will be expected to participate. They will explain the process of randomization, the three interventions being tested (DSMT, RGM, and CHW support), potential risk and benefit, and how risk will be mitigated. The research specialist will answer all participant questions and obtain a signature if the participant is still interested in participating in the study. All participants who provide a signature on the consent form will receive a copy to take home. This will detail the study activities and contact information for the principal investigators (PIs) and who to contact at Sinai Chicago with any additional questions or concerns.

### Additional consent provisions for collection and use of participant data and biological specimens {26b}

Not applicable. All consent provisions have been described above.

## Interventions

### Explanation for the choice of comparators {6b}

Appropriate diabetes management is essential to reduce diabetes-related morbidity and mortality among people living with diabetes. Diabetes management can include monitoring blood glucose, medication and appointment adherence, physical activity, healthy nutrition, and annual screenings which can include blood work, eye exams, and sensation testing of the extremities [21]. Being able to achieve proper diabetes management relies on both patient and provider factors. Patients may need social support services, access to health care services, and culturally and linguistically appropriate resources. Providers’ beliefs and attitudes of the disease, ongoing interactions and relationship between patient and provider, and internal environment of their health system can also contribute to patients’ diabetes self-management [22–24]. Given these factors, we selected three interventions for supporting diabetes management. First, DSMT, also known as diabetes self-management education and support (DSMES), is an education program for people living with diabetes that employs an evidence-based curriculum and has led to improved diabetes-related health outcomes [25]. Second, RGM refers to an automated process of transmitting blood glucose levels directly from a smart phone to a healthcare provider. Limited research exists, but those that do, have found regular engagement with technology like RGM have led to improved health outcomes [13]. Finally, in the second rerandomization we will include tailored support from a CHW. CHWs are frontline public health workers who are trusted members of and/or have a particularly close relationship with the community of interest [26]. Evidence has shown that CHWs can be a cost-effective way to improve chronic disease management and address the social determinants of health that underlie health inequities [27, 28].

### Intervention description {11a}

In the first randomization, study participants will be randomly assigned to either the DSMT or RGM study arms after completion of the enrollment and baseline data collection. At 6 months, they will attend an in-person appointment for HbA1c lab work (if it has been more than 3 months since their last HbA1c lab work) or HbA1c point of care testing. Depending on their HbA1c, they will continue in the first randomization arm, or they will be rerandomized. Each intervention is described below.

#### Diabetes self-management training

Participants who are randomized to a DSMT arm will be part of a small-group four-part diabetes education series. Groups will consist of 5–8 participants and will be led by a diabetes educator. Each session will take place in person, will be approximately 2 h in length, and will be offered at the same day and time, every other week. Cohorts will move together through the series. Classes will include (1) Overview and monitoring of diabetes, (2) Healthy eating and exercise, (3) Importance of diabetic medication, and (4) Living with diabetes. If participants are unable to attend a class, they will be offered a makeup class by joining the missed session of another cohort.

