### Sample size {14}

The sample size calculation, performed using G*Power (version 3.1), is based on the primary outcome of HbA1c over the 12-month study period, with the primary predictor being the six treatment conditions taken over the course of the study. The Null (H0) and Alternative (H1) Hypotheses are H0: There is no difference in the mean change in HbA1c among the six treatment groups, and H1: There is a significant difference in the mean change in HbA1c among the six treatment groups. The analysis assumes a significance level of 5%, 80% power, six treatment groups, equal group allocation, and a medium effect size of *f* = 0.25. The effect size of *f* = 0.25 was selected based on Cohen’s conventions for effect sizes in behavioral sciences, where 0.10 represents a small effect, 0.25 represents a medium effect, and 0.40 represents a large effect. A medium effect size is considered appropriate for this study, as it balances the detection of meaningful clinical differences with practical sample size considerations. Previous studies on diabetes management interventions such as DSMT and RGM have reported effect sizes in this range, indicating that a medium effect size is a reasonable expectation for interventions aimed at reducing HbA1c [13, 25].

The sample size estimation properly accounted for the multiple groups and comparisons inherent in the SMART design. Specifically, we conducted the sample size estimation for detecting a difference in HbA1c change across the six treatment groups, using an ANOVA framework, which inherently accounts for multiple comparisons. To ensure robustness and accommodate potential dropouts, we inflated the sample size by 20%. Thus, the minimum required sample size is 216 patients, and to account for an anticipated dropout rate, we aim to recruit 270 patients. This approach ensures that the study is adequately powered to detect significant differences across all treatment conditions, providing a solid basis for our subsequent analyses.

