#### Primary outcomes

To optimize the adaptive intervention and understand the causal effects of each proposed sequence, we will employ a SMART design. This design is particularly advantageous for chronic diseases like diabetes, where there is significant heterogeneity in response to treatment. The SMART design allows for re-randomization based on a tailoring variable, which in our study is the change in HbA1c at 6 months, enabling patients to receive an adaptive intervention that is most suited to their needs. To address potential imbalances in randomization, we will use stratified and block randomization techniques.

For primary analysis, we will employ linear regression models adjusting for baseline characteristics utilizing type III sum of squares to account for these discrepancies. Sensitivity analyses will include inverse probability weighting to account for any imbalances. To assess the overall HbA1c reduction by treatment condition and the average patient percentage point reduction in HbA1c from baseline to 12 months within each of the six treatment conditions, we will utilize one-way ANOVA for mean comparisons, followed by pairwise comparisons with a Tukey post hoc test to correct for multiple comparisons. In cases of non-normal data distribution, we will opt for Kruskall-Wallis tests and a Dunn post hoc test with Hommel multiple comparison *p*-value corrections.

Linear regression will be employed to adjust for additional covariates that may confound the relationship between treatment and outcome, such as baseline characteristics with residual confounding post-randomization, and baseline and 6-month HbA1c values. We will also test for possible interactions of covariates with the treatment variable, reporting model adjusted slopes (β_ADJ_), 95% confidence intervals, model diagnostics, and goodness of fit (via R^2^).

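### DSMT is taught in cohorts of 5 to 8, but the named tests and the sample size treat participants as independent; if cohort outcomes correlate, the six-group test and some DSMT contrasts exceed their nominal 5%

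*Protocol article*

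**What the plan says.** **Delivery.** The protocol article, under Diabetes self-management training, states: "Participants who are randomized to a DSMT arm will be part of a small-group four-part diabetes education series". It adds: "Groups will consist of 5–8 participants and will be led by a diabetes educator". There are four in-person sessions of about two hours, one every other week, and "Cohorts will move together through the series". Anyone who misses a class may cross over for that session: "they will be offered a makeup class by joining the missed session of another cohort". By contrast, the sections on remote glucose monitoring and community health worker support describe one-to-one set-up, education and follow-up. The design is therefore partially nested: DSMT participants sit in groups and the others do not.

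**Analysis.** Under Primary outcomes in section {20a}: "For primary analysis, we will employ linear regression models adjusting for baseline characteristics". The same section names one-way ANOVA across the six conditions with Tukey comparisons, and Kruskal-Wallis with Dunn comparisons as the fallback. Under Secondary outcomes, between-group survey scores are compared by independent t-tests or Mann–Whitney tests. None of these is given a cohort term.

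**Sample size.** Section {14} states: "The analysis assumes a significance level of 5%, 80% power, six treatment groups, equal group allocation, and a medium effect size of" f = 0.25. The calculation is made "using an ANOVA framework, which inherently accounts for multiple comparisons". That phrase concerns multiplicity, but the framework is an ANOVA on individuals, and the only inflation described is for dropout. The document mentions no ICC, design effect, mixed model or cluster-robust variance.

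**The concern.** People who go through four classes together share a time slot, class discussion and whatever went well or badly in that group. If this leaves any trace in HbA1c, two members of one cohort resemble each other more than two members of different cohorts. The mean of a DSMT group then varies more than an independent-observations formula allows.

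Where the extra variance does not cancel, the plan's standard errors are too small, its confidence intervals too narrow, and its real type I error above the stated 5%. The affected tests include the six-group comparison on which the trial is sized. For the same reason, the stated 80% power holds only if there is no cohort correlation.

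This is not merely detail left to an analysis plan: the protocol itself fixes the tests and the sample-size method.

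**Working it through.** **1. The plan's own figure.** Inputs from section {14}: k = 6, α = 0.05, f = 0.25, power 0.80. With noncentrality λ = N·f², the smallest N is 211 (power 0.800). Rounded up to equal groups this is 216, or 36 per path, with power 0.811. Allowing for 20% dropout, 216/(1 − 0.20) = 270. Both stated numbers reproduce, under independence.

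**2. Assumptions added.** The documents give no ICC, so 0.01 to 0.10 is an assumed range. Cohort size m is 5 to 8, as stated. There are 216 analysed: 108 DSMT-first, 108 RGM-first and 36 per path. Response is taken as unrelated to cohort.

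**3. Design effect for pooled DSMT-first participants.** DE = 1 + (m − 1)·ICC.
- ICC 0.01: 1.04–1.07
- ICC 0.02: 1.08–1.14
- ICC 0.05: 1.20–1.35
- ICC 0.10: 1.40–1.70

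For pooled DSMT versus RGM, only one side is inflated. The true SE over the naive SE is √((DE + 1)/2), and type I error is 2·(1 − Φ(1.96/ratio)). At ICC 0.05 and m = 8: √(2.35/2) = 1.084, giving 7.1%.

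**4. Why single paths differ.** DSMT-first cohort members are spread over three paths, so a member of a 36-person path shares that path with only about 35/107 = 0.327 of his or her cohort-mates. The path-level design effect is about 1 + 0.327·(m − 1)·ICC. At ICC 0.05 and m = 8 this is 1 + 0.327 × 7 × 0.05 = 1.114. Against an unclustered path the SE ratio is √(2.114/2) = 1.028 and type I error is 5.7%. Between two DSMT-first paths, the shared cohort effects appear on both sides and almost exactly cancel.

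**5. Simulation under the null.** 100,000 replicates per cell; each range runs from m = 5 to m = 8; values are % type I error at nominal 5%.

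| ICC | Six-group ANOVA | Pooled DSMT vs RGM | RGM-to-DSMT vs RGM-to-CHW | DSMT-to-CHW vs RGM-to-CHW | DSMT-to-CHW vs DSMT-to-RGM |
|---|---|---|---|---|---|
| 0.01 | 5.2–5.5 | 5.1–5.4 | 5.2–5.3 | 5.0–5.1 | about 5 |
| 0.02 | 5.5–5.9 | 5.4–5.7 | 5.4–5.9 | 5.1–5.2 | about 5 |
| 0.05 | 6.2–7.2 | 6.1–7.0 | 6.1–6.8 | 5.4–5.7 | about 5 |
| 0.10 | 7.6–9.8 | 7.4–9.1 | 7.4–9.0 | 5.8–6.4 | about 5 |

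**6. Dropout.** If 20% are lost, a mean enrolled cohort of 6.5 leaves 6.5 × 0.80 = 5.2 analysed. By the formulas in step 3, the pooled contrast then has DE 1.08, 1.21 and 1.42 and type I error 5.5%, 6.2% and 7.5% at ICC 0.02, 0.05 and 0.10. At 6.5 analysed per cohort the errors would be 5.6%, 6.6% and 8.3%. Realistic values therefore lie towards the lower end of each range.

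**7. Power, roughly.** Deflate the DSMT-first half: N_eff = 108/DE + 108. At ICC 0.05 this is 108/1.20 + 108 = 198 to 108/1.35 + 108 = 188, with ANOVA power 0.77 to 0.74. At ICC 0.10, power is 0.74 to 0.70. This is an approximation, because one design effect does not apply evenly across the six groups.

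**The case against.** **The correlation may be close to nil.** The outcome is HbA1c change at 12 months, long after a short class series, and non-responders are individually re-randomised in between. Section {23} lists one diabetes educator; if that person teaches every cohort, differences between educators add nothing. Make-up classes blur cohort membership. All of this stands, and it is why the size is given as a range starting at an almost harmless 0.01. It does not show that the ICC is zero, since shared timing and group discussion remain.

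**A reader might infer that every contrast with DSMT on one side, or every planned test, is too liberal.** The documents do not support that. DSMT-to-CHW against DSMT-to-RGM stays at about 5%, and DSMT-to-CHW against RGM-to-CHW is 5.4–5.7% even at ICC 0.05. The stated hypothesis, that DSMT-to-CHW beats all other paths, rests partly on such contrasts. The inference is also not available for Q-learning and g-estimation, because no variance estimator is stated for them.

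**The pooled first-stage contrast is not a named 5% test.** This is correct: the primary comparison is across six conditions, and the first stage enters through Q-learning. The six-group column is therefore the one to rely on, and it shows inflation of the same order.

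**A separate analysis plan is promised and could add a random effect.** It could, but it would then have to depart from the methods and the power statement the protocol already fixes.

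**Conclusion.** The concern holds in a limited and conditional form. If outcomes correlate within DSMT cohorts, the plan as written understates the variance for three comparisons: the six-group test, a pooled first-stage DSMT versus RGM contrast, and RGM-to-DSMT against another RGM-first path. Comparisons between DSMT-first paths are essentially sound, and single DSMT-first against RGM-first paths are only slightly affected.

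The effect on the six-group test is negligible at an ICC of 0.01 and becomes material from about 0.05. The figures assume equal path sizes, response unrelated to cohort, and stable membership. A reader might take it as established that the standard errors are too small; the documents give no ICC and so support only the conditional statement. The point should be corrected, but it does not threaten the trial.

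**What to change.** - Record the original DSMT cohort as a field in REDCap. DSMT attendance sheets are already a data source, so it should be recoverable for people already enrolled. Keep it for all DSMT-first participants whatever their second-stage path, and assign it to those switched to DSMT. People who take a make-up class stay in their original cohort.
- Fit the primary model with a cohort random intercept for DSMT participants only, everyone else being a cluster of one, with small-sample degrees of freedom. Alternatively, use cluster-robust standard errors on the same clusters with a small-sample correction. The correction matters: 36 people switched to DSMT form only about 36/8 to 36/5, or roughly 5 to 7, cohorts.
- Use the same clustering for the between-group survey comparisons.
- Report the estimated ICC.
- Restate the 80% power in section {14} as holding only without cohort correlation, with about 0.74–0.77 at an ICC of 0.05.

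The cost is one data field, a changed model statement and slightly wider intervals. The fix needs no extra patients, but it accepts the lower power. Holding power at ICC 0.05 would take roughly 216 × (1 + DE)/2 = 238 to 254 analysed, or 298 to 318 recruited after 20% dropout.

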#### Remote glucose monitoring

Participants who are randomized to the RGM arm will work with a study team member to download and set up a profile with the Glooko application on their personal smartphone device at the time of enrollment. Participants will receive a 1-h education session, where a study team member will assist with downloading the Glooko application, sync their Glooko-compatible meter, insulin pump, or continuous monitoring device, and provide education on Glooko’s features. After the education session, the participant will be instructed to use the application over the next 6 months. Participant glucose levels will be automatically transmitted to the electronic medical record (EMR), where providers can monitor the data remotely. The participant will also be able to track their weight, blood pressure, exercise, log food and meals, set reminders, and make notes on the application. Participants are provided with the research team’s contact information in case technical support is needed. The research team will also reach out to each participant every 2 months to provide technical assistance and encourage engagement with the application.

#### Community health worker support

CHWs will be introduced 6 months into the trial at rerandomization for participants whose HbA1c has not improved by at least one percentage point (Fig. 2. IDEA Study SMART Design). All patients paired with a CHW will be screened for social needs utilizing a standard social determinants of health (SDoH) screening tool, will receive referrals to resources to address unmet social/health needs, and will be actively navigated to health and social service resources as appropriate.

For participants originally randomized to the RGM intervention, the CHWs will focus on enhancing uptake and use of the Glooko application. During the initial in-person visit with the CHW, which will take place either at the clinic or in the participant’s home, the CHW will screen for SDoH needs, provide referrals to address unmet needs, and assess participant barriers to regularly measuring and/or reporting glucose levels using Glooko (e.g., connection issues between device and phone, barriers to transmitting information to provider). The CHW will also support the patient in overcoming barriers through individualized education, motivational interviewing, goal-setting, and trouble-shooting technological and resource challenges. Following the initial visit, the CHW will follow up with the patient at least monthly by phone for 6 months to assess adherence with RGM, trouble shoot additional barriers, and reinforce education concerning the Glooko application. The CHW will also provide active support to the participant in connecting with resources to support health and social needs. Additional in-person visits will occur during the time interval as needed.

For participants originally randomized to the DSMT study arm, the CHW will focus on reinforcing key messages presented during DSMT sessions. During the initial in-person visit with the CHW, which will take place either at the clinic or in the participant’s home, the CHW will screen for SDoH needs, provide referrals to address unmet needs, and assess knowledge gained during the group DSMT sessions, self-efficacy to manage diabetes, and application of learnings. The CHW will support the patient in overcoming deficits in knowledge and barriers in application of knowledge via additional customized, one-on-one education sessions, motivational interviewing, goal-setting, and navigation support. Following the initial visit, the CHW will follow-up with the patient at least monthly by phone, scheduling additional in-person visits as needed for up to 6 months. Additional in-person visits will occur during the time interval as needed.

